## Abstract

**Background:**

Tai Chi Chuan (TCC) is a physical activity modality that originated in China and is now widely popular around the world. Although there are a series of articles reporting that TCC can improve balance and other functional symptoms in a variety of populations, including the elderly, patients with stroke, and patients with Parkinson's disease, its efficiency has not been scientifically and methodically evaluated in subjects with functional ankle instability (FAI). Moreover, there is no literature directly comparing TCC and conventional balance training (CBT) interventions for FAI. The objective of this study is to investigate the comparative effects of TCC intervention and CBT protocols in improving postural balance and subjective instability feelings in patients with FAI.

**Discussion:**

This trial will demonstrate whether a 12-week TCC intervention positively affects postural stability and self-reported outcomes in patients with FAI. At the same time, the superiority of its clinical efficacy will also be compared with that of CBT. This study may also help to redefine the value of traditional Chinese exercises in the treatment of chronic ankle instability.

**Clinical trial registration:**

Chinese Clinical Trial Registry: ChiCTR2100041790. Registration date: 22 March 2021. http://www.chictr.org.cn/edit.aspx?pid=119501&htm=4.

## Background

Ankle inversion sprain is one of the most common injuries suffered in both sportsmen and physically active individuals (1). It has been reported that the recurrence rate of a lateral ankle sprain after the initial injury is as high as 80% (2). Recurrent ankle sprains often result in residual symptoms and often lead to the development of functional ankle instability (FAI) (3). FAI is one of the leading causes of people's daily activity disorders, which is characterized by recurrent ankle instability, a feeling of “giving way,” persistent ankle pain, and self-reported disability (4, 5). The pathogenesis of FAI is thought to be associated with mechanical impairment, neuromuscular, and sensorimotor deficiencies, such as decreased proprioception, strength deficits, and motor neuron excitability (6, 7). All these symptoms can lead to postural control impairment and ankle instability in patients with FAI, severely affecting mobility and quality of life in patients with FAI (8–10).

Balance ability refers to the ability of the human body to maintain the stability of the center of gravity in the process of static and dynamic movement, and the decline of balance ability will increase the instability of the ankle and risk of ankle injury (11). Previous studies have shown that balance training, proprioceptive exercise, and manual therapy can be used to improve ankle function and increase ankle stability (12–14). Among these, balance training is a widely used intervention in clinical practice which can improve posture control ability, motor ability, proprioception function, and increase the stability of ankle joints (13).

Tai Chi Chuan (TCC) is a traditional Chinese exercise form known for its slow and graceful movements, which is widely used around the world. TCC emphasizes abdominal breathing, waist axis driving limb movement, virtual and real conversion of center of gravity, and coordinated swing of hip/knee/ankle to improve body stability, as well as forward and backward stepping movements to increase the ranges of dorsiflexion and plantarflexion (15). Studies have shown that the practice of this physical activity can produce a series of beneficial effects, such as improvement of proprioception, activation of core muscle groups, and improvement of muscle strength around joints, all of which may have a positive impact on patients with chronic ankle instability (CAI) (16, 17). Although self-reported improvements in functional status, postural balance, and lower extremity strength have been demonstrated in response to TCC, to the best of our knowledge, there is still a lack of effective evidence that postural control improvements occur as a result of practicing TCC in individuals with FAI.

As far as we know, only one research group has reported that TCC intervention has a positive effect on postural control and self-reported instability feeling in patients with CAI but failed to compare the clinical effects with other training programs (18). Moreover, there is no literature directly examining the comparative effects of TCC intervention and conventional balance training (CBT) protocols regarding their impact on postural stability and self-reported outcomes in patients with FAI. From the perspective of clinical utility, it is extremely interesting to see which intervention is more effective as clinicians always want to be able to select the best intervention for patients with FAI. Theoretically, patients with FAI are a series of complex clinical syndromes resulting from the interaction of pathomechanical, sensory perceptual, and motor behavior impairments (19, 20). Balance training alone may only achieve partial therapeutic effects. TCC is a kind of mind–body exercise that may be particularly beneficial to FAI because it involves movement recall, task switching, attention, and visuospatial processing simultaneous with physical movements (21). Therefore, our hypothesis is that both TCC intervention and CBT would obtain significant improvements, with a possible superiority of TCC over CBT. Thus, the aim of this randomized controlled study is to test the comparative effects of TCC intervention and CBT protocols in improving postural balance and subjective instability feelings in patients with FAI.

## Methods and analysis

### Study design and setting

This study will be a single-center, randomized, exploratory trial with two parallel groups. The objective is to test the comparative effects of TCC intervention and CBT protocols in improving postural balance and subjective instability feelings in patients with FAI.

We recruited subjects from the Fujian Provincial Hospital, the surrounding Sports Center, and residents of Gulou District, Fuzhou City, Fujian Province, China. Potential eligible subjects who meet the following inclusion criteria but are excluded from the exclusion criteria will be determined by two orthopedic surgeons for eventual inclusion in the study. After signing the written informed consent form, eligible participants will be randomly divided into two groups, the intervention group or the control group, at a 1:1 ratio. All assessments will be conducted at baseline, post intervention, and 3-month follow-up. This study was designed in strict accordance with the Standardized Protocol Items, including the Recommendations for Interventional Trials (SPIRIT) Checklist, and has been approved by the Ethical Committee of Fujian Provincial Hospital (no. k2019-03-035). In addition, we have completed registration in the Chinese Clinical Trials Registry in 2021. The flow diagram for this trial is shown in Figure 1. The specific flowchart of participant recruitment is shown in Table 1.

**Figure 1 F1:**
[figure not shown]
Flow diagram of participants.

**Table 1 T1:** Trial processes chart.

**Items**	**Before enrollment−2 to 1 (week)**	**Intervention period 1−12 (week)**	**Outcome assessment 13 (week)**	**3-month follow-up**
Inclusion criteria	√			
Exclusion criteria	√			
Informed consent	√			
Baseline	√			
Randomization and allocation	√			
Intervention		√		
Static balance tests	√		√	√
Dynamic balance tests	√		√	√
CAIT	√		√	√
AOFAS-AHES	√		√	√
SF-36	√		√	√
Adverse events		√		
Reasons of drop-out and withdrawals		√		

### Inclusion criteria

Participants who meet the following criteria will be included: (1) a history of one or more lateral ankle sprains within at least 6 months prior to the participation in this study; (2) a score on the Cumberland Ankle Instability Tool (CAIT) that is ≤ 25 points ensures a sense of ankle instability; (3) no history of other bone, muscle, and joint injuries of lower limbs; (4) no history of other neurological diseases, such as those that alter cognition, ataxia, and balance dysfunction; (5) pain in the ankle below the mild level, visual analog scale (VAS) ≤ 3; (6) those physically active and able to maintain their activity level regardless of their FAI status; and (7) those willing to participate and signed the informed consent form.

### Exclusion criteria

Participants who meet the following criteria will not be included in this study: (1) those with particular diseases in addition to ankle instability; (2) those who have experienced ankle joint surgery in the past; and (3) those who have participated in an ankle rehabilitation program 6 weeks prior to this study.

### Withdrawal from the study

In any of the following cases, participants will be allowed or asked to withdraw from the study:

(1) Those unwilling to continue participation in the experiment for any reason no matter at what stage of the trial.(2) Those who experience an adverse event (AE) that it is not suitable for continued participation in the trial.(3) Participants absent from TCC training too many times and not suitable for continued participation in the trial.

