### Experimental group

On the basis of health education treatment in the control group, the TCC intervention group will undergo a 40-min 24 Simplified Yang-style TCC exercise. Yang-style TCC consists of slow, smooth, and rhythmic movements that emphasize the practitioner's focus on trunk rotation, weight shifting, coordination, and maintenance of lower limb posture stability. Subjects with FAI will be taught and supervised by an expert TCC coach to ensure the unity of practice time and the basic correctness of action rhythm. The complete set of TCC exercises consists of three parts: 5-min warmup, 30-min TCC practice, and 5-min cool down. Practice will occur once per day, three times a week for 12 weeks, for a total of 36 times.

During the whole training process, patients are encouraged to keep practicing if they have slight ankle pain. If the ankle joint pain of the subject is obvious during the training, i.e., VAS > 3 points, we will suggest the subject to rest or suspend the training, and continue after the pain is relieved.

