### Assessment of safety

TCC is a traditional sports event in China. As it is a non-invasive intervention method and the TCC in this study is conducted under the guidance of an expert coach, its standardization and safety are sufficiently guaranteed. Nevertheless, during the study period, if the subject has any discomfort, or new changes to their condition, or any unexpected circumstances, whether related to the study or not, relevant information will be recorded in detail in the case report forms (CRFs). At the same time, researchers will identify the relevance of AEs to clinical interventions. In case of adverse reactions, the clinician will comprehensively evaluate the subject's condition and then decide whether to stop the trial. If any serious adverse event (SAE) occurs, emergency medical assistance will be sought.

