### Data analysis

Statistical analysis will be carried out using SPSS Statistics, version 22.0 (SPSS Inc., Chicago, IL, USA). All assigned subjects with available data will be analyzed according to the intention-to-treat principle. Continuous variables, such as CAIT score, age, and disease duration, will be expressed as mean ± standard deviation (SD) or medians (25th to 75th centiles), depending on whether the distribution of variables is normal or skewed. For other categorical data, we will use Mann–Whitney test, chi-square test, or Fisher's exact test for statistical analysis as appropriate. Multiple-measure variables will be analyzed by repeated-measures ANOVA. Additionally, we will use the last-observation-carried-forward method to deal with the missing data. Statistical significance will be assessed as *p* < 0.05.

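### The adverse-event withdrawal rule takes participants out of the study, not only out of training, so their later CAIT would be missing or replaced by the baseline score

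*Protocol article*

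**What the plan says.** The section Withdrawal from the study opens: "In any of the following cases, participants will be allowed or asked to withdraw from the study". Its second case is "Those who experience an adverse event (AE) that it is not suitable for continued participation in the trial". Assessment of safety uses similar language: after an adverse reaction, "the clinician will comprehensively evaluate the subject's condition and then decide whether to stop the trial". Both passages speak of the study or trial, not of the exercise sessions.

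The protocol can make the distinction when it wants to. Under Experimental group, for pain above VAS 3 during Tai Chi training, "we will suggest the subject to rest or suspend the training, and continue after the pain is relieved".

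Five other places bear on the point:

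- **Sample size** gives an expected withdrawal rate of 10–20% and raises the total from 56 to 68.
- **Study design and setting** and **Table 1** place outcome assessments at baseline, week 13 and 3 months, with none in between.
- **Table 1**, **Assessment of safety** and **Data management and monitoring** provide for recording adverse events and withdrawals.
- **Data analysis** states: "All assigned subjects with available data will be analyzed according to the intention-to-treat principle". It adds that missing data will be handled by LOCF.
- **Randomization and blinding** says that clinicians and therapists know the allocation.

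**The concern.** An intention-to-treat comparison needs outcomes from everyone randomised, including those who stop treatment. If an adverse event ends study participation, whether an outcome exists depends on something that happened after randomisation and that the allocated programme may have caused. The judgement is also made by a clinician who knows the arm.

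In ankle instability, an event serious enough to end participation, such as a re-sprain, could well be a poor result on CAIT, which the protocol names as a primary outcome. These are therefore outcomes that the trial can least afford to lose, and ordinary analysis of the remaining data does not recover them. At stake is whether each arm's mean CAIT change reflects all who were assigned to it.

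**Working it through.** **Does the protocol expect outcomes from those who withdraw?** No section says so either way. The sample-size step is the best evidence. Per arm, 28 × 1.2 = 33.6, rounded up to 34, so 68 in total. With 68 enrolled, 56 remain if 12 are lost (12/68 = 17.6%), within the stated 10–20%. Enrolling 12 more people to cover withdrawals makes sense only if those who withdraw are counted as giving no analysable outcome.

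**What happens to someone who leaves during weeks 1–12?** Data analysis allows two readings:

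- Limiting the analysis to subjects with data leaves the person out.
- LOCF carries the last value forward. As nothing is measured between baseline and week 13, that value is the baseline score, so the recorded change is 0.

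Someone who leaves after week 13 would carry the week-13 value to 3 months.

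**Illustrative size.** From the documents: 34 per arm. Assumptions, because the documents give no such figures: *k* = 1 to 3 people in one arm leave for an adverse event, their true CAIT change *t* is -3 or -5, and the others gain *g* = 8.

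- True arm mean = [(34 − k)g + kt]/34
- Mean under LOCF = (34 − k)g/34, so the overstatement is −kt/34
- Mean if omitted = g, so the overstatement is k(g − t)/34

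| k | t | True mean | LOCF mean | LOCF overstates by | Omission overstates by |
|---|---|---|---|---|---|
| 1 | -3 | 7.68 | 7.76 | 3/34 = 0.09 | 11/34 = 0.32 |
| 1 | -5 | 7.62 | 7.76 | 5/34 = 0.15 | 13/34 = 0.38 |
| 3 | -3 | 7.03 | 7.29 | 9/34 = 0.26 | 33/34 = 0.97 |
| 3 | -5 | 6.85 | 7.29 | 15/34 = 0.44 | 39/34 = 1.15 |

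With the protocol's planning gain of 10.8 in place of 8, and t = -3, omission overstates by 13.8/34 = 0.41 (k = 1) to 41.4/34 = 1.22 (k = 3). The LOCF figures do not depend on g. For scale, 10% of 34 is 3.4, so k = 3 lies below the lower end of the protocol's own allowance for withdrawals of all causes.

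**Yardsticks.** The CAIT planning SDs of 2.21 and 2.10 give a pooled SD of √[(2.21² + 2.10²)/2] = 2.156, so the planned effect of 0.8 SD is 1.72 points. LOCF overstatement is then 5% to 26% of it (0.09/1.72 to 0.44/1.72), and omission 19% to 67% (0.32/1.72 to 1.15/1.72). Against the planning difference in means, 10.8 − 0.2 = 10.6 points, the largest LOCF figure is 0.44/10.6 = 4%.

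**Between arms.** The bias in the difference is the overstatement in one arm minus that in the other. With equal numbers and equal losses it is zero. The rule covers both arms, and no expected event rates are given.

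**The case against.** The strongest reply is that this is a condensed article that nowhere says assessment ends at withdrawal, and that the wording permits or requests withdrawal without requiring it. A reader might infer that these participants are never measured. The documents do not say that. What they contain is a stated rule that ends study participation, a sample size that counts on losing those who withdraw, and no provision to keep assessing them. That is enough to ask for a change, but not to assert that follow-up will stop.

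Three other strong readings also fail:

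- **That the trial omits harm.** It does not. Adverse events and withdrawals are to be recorded, the events whether or not they are related to the study. What may be lost is the later efficacy score.
- **That everyone who is hurt is removed.** Only events judged incompatible with continuing fall under the rule. In the Tai Chi arm, pain above VAS 3 leads to a pause and a return.
- **That removal makes the more harmful programme look better by the full omission figure.** LOCF is the stated method. If it is applied to these people, the smaller range holds. If someone had improved before leaving, carrying baseline forward would understate that arm's mean.

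The objection that the shift is small also has force. Even 0.44 points is well below the 3-point minimum detectable change that the protocol cites. That threshold concerns the change in a patient, however, not bias in a group mean. Nor is 10.6 points a safe yardstick: the Background says that the earlier Tai Chi study made no comparison with another training programme, and this protocol expects both arms to improve.

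**Conclusion.** The point holds in a limited form. As written, an adverse event judged incompatible with participation is a reason to leave the study, and nothing keeps the participant in outcome assessment. The post-event CAIT is then either absent or replaced by a pre-event value, and the Data analysis section does not settle which. Both routes hide worsening, which sits badly with the promise of intention-to-treat.

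The size is modest: roughly 0.09 to 0.44 points on one arm's mean under LOCF, and 0.3 to 1.15 if these people are left out. It rests on assumed numbers of events and assumed true changes, with all events placed in one arm. The documents give no basis for saying which arm would benefit. The change is still worth making, because it is cheap and because measurements not taken cannot be recovered later.

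**What to change.** Leave the clinical decision to stop training as it is, and change only its consequence. Reconcile Withdrawal from the study, Assessment of safety and Data analysis so that they say the following:

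- A participant who stops training because of an adverse event stays in follow-up unless consent to follow-up is withdrawn. Stopping training and leaving follow-up are recorded as separate events.
- CAIT and SF-36 are sought at week 13 and 3 months, by telephone if the participant cannot attend. The platform tests and the physician-assessed part of AOFAS-AHES still need a visit and may remain missing.
- These participants are analysed in the arm to which they were randomised. The text states whether a person with no post-baseline score is included under LOCF or left out.

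The cost is protocol and consent wording and a few extra questionnaires. No additional participants or procedures are needed.

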### Sample size

Sample size calculations were done using the G-power 3.1.9.2 software (developed by the University of Düsseldorf, Germany). An effect size of 0.8 and a two-sided alpha level of 0.05 were set based on the differences of pre- and post-treatment repeated measurement points of Star Excursion Balance Test (SEBT) and CAIT; a total sample of 56 participants (28 patients in each group) is required to achieve 90% power. The estimated withdrawal rate was 10–20%, and a total of 68 participants (34 patients in each group) were planned to be enrolled in this clinical trial. The power analysis is based on the primary outcome variable, including within-group differences in SEBT and CAIT (dependent variables) before and after treatment. The means and standard deviations of the SEBT and CAIT are based on the results from a similar published study from Spain (18) and preliminary experiment of the research group (intervention group: ▴SEBT-posteromedial M = 6.46, SD = 6.89, ▴CAIT M = 10.8, SD = 2.21, control group: ▴SEBT-posteromedial M =0.64, SD = 3.86, ▴CAIT M =0.2, SD = 2.10), with a 1:1 allocation ratio.

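### The 56 participants stated for 90% power at effect size 0.8 give about 84% with the stated two-sided test, and the 68 enrolled leave no allowance for withdrawals

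*Protocol article*

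**What the plan says.** All of this is in the Sample size section of the protocol article.

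- **Software:** "Sample size calculations were done using the G-power 3.1.9.2 software".
- **Effect size and alpha:** "An effect size of 0.8 and a two-sided alpha level of 0.05 were set based on the differences" between pre- and post-treatment measurements of the SEBT and the CAIT.
- **Result:** "a total sample of 56 participants (28 patients in each group) is required to achieve 90% power".
- **Allowance for loss:** "The estimated withdrawal rate was 10–20%, and a total of 68 participants (34 patients in each group) were planned to be enrolled".
- **Supporting data:** change scores for both groups, "with a 1:1 allocation ratio". SEBT-posteromedial is 6.46 (SD 6.89) against 0.64 (SD 3.86), and CAIT is 10.8 (SD 2.21) against 0.2 (SD 2.10).

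The section does not name the statistical test. It describes the basis as within-group change but gives data for two groups. The trial's stated aim, in the Background and in Study design and setting, is to compare the two interventions.

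**The concern.** An effect size of 0.8, two-sided alpha 0.05, 90% power and equal groups fully determine the size of a two-group t-test comparison. The answer is well above 28 per group. If 56 is too small, the 68 presented as an inflated number is not inflated at all.

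What is at stake is how the result will be read. A reader of a null comparison would assume that a true 0.8 SD difference had a 10% chance of being missed. If the real figure is nearer 13–18%, the null result is weaker evidence than the article implies.

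**Working it through.** **Inputs (all from Sample size):** d = 0.8; alpha = 0.05, two-sided; power 90%; allocation 1:1; stated n = 28 per group; enrolled n = 34 per group; withdrawal 10–20%.

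**Formula.** For a two-sample t-test with n per group, the noncentrality is δ = d·√(n/2) and the degrees of freedom are 2n − 2. Power is the probability that a noncentral t variable with these parameters exceeds the critical value (in either tail for a two-sided test).

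**1. Trying to reproduce 56.** At n = 28, δ = 0.8 × √14 = 2.993 with 54 degrees of freedom.

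| Test | Critical t | Power at 28 per group | n per group for 90% |
|---|---|---|---|
| Two-sided 0.05 (as stated) | 2.005 | 83.6% | 33.8, so 34 (68 in total) |
| One-sided 0.05 | 1.674 | 90.5% | 27.5, so 28 (56 in total) |

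The stated inputs do not give 56. Changing only the sidedness gives it exactly. At 34 per group the two-sided power is 90.2%.

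**2. Other routes to 56.**

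- Paired t-test with a standardised change of 0.8: 18.4, so 19. This is not 28, so the within-group wording does not explain the figure.
- Wilcoxon–Mann–Whitney, two-sided: 36 per group.
- Bonferroni alpha of 0.025 for two outcomes: 41 per group.
- ANCOVA: about 28 per group, but only with a baseline correlation of about 0.4, which the article does not give.
- Between-group effect in a repeated-measures ANOVA, with d = 0.8 entered as f = 0.4: 56 in total if the correlation is 0.6 with two time points or 0.7 with three. At correlation 0.5 it gives 52 or 46, and at 0.8 it gives 62 or 60. The article states neither f nor a correlation.

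**3. Power after the stated withdrawals, two-sided, d = 0.8.**

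| Withdrawal | Evaluable of 68 | Power | d detectable with 90% power |
|---|---|---|---|
| 0% | 68 | 90.2% | 0.80 |
| 10% | 68 × 0.9 = 61.2 | about 87% | 0.84 |
| 20% | 68 × 0.8 = 54.4 | about 82% | 0.90 |

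The chance of missing a true 0.8 SD difference is therefore about 13% to 18%.

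**4. The withdrawal allowance on its own terms.** Taking 56 as correct, the number to enrol is 56/(1 − 0.10) = 62.2, so 63, up to 56/(1 − 0.20) = 70. The planned 68 falls short at the upper end: 34 × 0.8 = 27.2 per group, below 28. The figure 68 agrees with 56 × 1.2 = 67.2 rounded up to equal groups, which is multiplication by 1 plus the loss rate instead of division by 1 minus it. This shortfall does not depend on which test was used.

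**The case against.** **The test is not named, so one-sided use is an inference.** This is correct. Data analysis plans repeated-measures ANOVA, and step 2 shows that such a model can reach 56. It does so only with a conversion to f = 0.4 and a particular correlation, neither of which is stated. The one-sided t-test needs one setting changed. It remains the likely explanation rather than a proven one. Whatever the cause, the stated inputs do not give 56 for a two-sided two-sample t-test.

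**If 56 were right for another model, 68 would cover most of the range.** It would cover a loss of 1 − 56/68 = 17.6%, and at 20% the shortfall would be one participant per group. On that reading the withdrawal gap is small. On the stated inputs it is the whole allowance.

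**The article's own data imply larger effects.** The pooled SD for SEBT is √((6.89² + 3.86²)/2) = 5.58, so d = 5.82/5.58 = 1.04, and for CAIT d is about 4.9. At d = 1.04, two-sided power is about 96% even with 27 per group. That is true, but the 90% claim is made for 0.8. The quoted control-group changes are also close to zero, whereas the Background expects the active comparator to produce significant improvement and TCC to be only possibly superior. The larger effects are not a safe cushion.

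**Last observation carried forward keeps withdrawals in the analysis.** The analysed number may then stay above 54–61. Carrying a value forward supplies no post-treatment information, so it does not restore power for a true 0.8 effect.

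**The trial calls itself exploratory, and the error does not bias the estimate or inflate type I error.** Both statements are right. The article nevertheless makes a specific power claim, and that claim should be correct.

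**Conclusion.** The point holds. With effect size 0.8, two-sided alpha 0.05 and equal groups, 90% power requires 34 evaluable participants per group, not 28. Two-sided power at 56 is 83.6%. The 68 enrolled equal the complete-data requirement and leave nothing for withdrawals; at the stated 10–20% loss, power is about 87% to 82%.

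This rests on reading 0.8 as a standardised between-group difference tested by an unadjusted two-sample t-test, and on withdrawals contributing no outcome information. That a one-sided setting produced 56 is well supported by the exact match but is not documented. Separately, and whatever the test, 68 does not meet a 20% withdrawal allowance on 56, which needs 70.

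**What to change.** Keep 68 randomised and the two-sided test. Delete the statement that 56 participants give 90% power, and replace the calculation with wording such as:

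> For a two-sample t-test of the between-group difference at two-sided alpha 0.05 and d = 0.8, 68 evaluable participants (34 per group) give 90% power. With 10–20% withdrawal (61 to 54 evaluable), power is about 87% to 82%; 90% power is then reached for d of 0.84 to 0.90.

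Do not move to a one-sided test to rescue the figure. If another model was in fact used to obtain 56, state the test, its effect measure and the assumed correlation, and correct the withdrawal arithmetic.

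The cost is a wording change and a less favourable stated power, with no additional participants. Holding 90% power at d = 0.8 after withdrawals would instead require 68/0.9 = 75.6, so 76 enrolled, at 10% loss, and 34/0.8 = 42.5, so 43 per group (86 in total), at 20%. Correcting the claim does not require that increase.
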